**Table 2. Prohibited and Rescue Medications**

| Prohibited medication/class of drug:                                                                                                                                                                                  | Usage:                                                                                                                                                                                                                                                                                  |
|------------------------------------------------------------------------------------------------------------------------------------------------------------------------------------------------------------------------------|------------------------------------------------------------------------------------------------------------------------------------------------------------------------------------------------------------------------------------------------------------------------------------------------|
| Additional investigational anticancer therapy concurrent with those under investigation in this study                                                                                                                        | Should not be given whilst the patient is on IP treatment                                                                                                                                                                                                                                      |
| mAbs against CTLA-4, PD-1, or PD-L1                                                                                                                                                                                          | Should not be given whilst the patient is on IP treatment through 90 days after the last dose of IP.                                                                                                                                                                                           |
| Any concurrent chemotherapy, local therapy (except palliative radiotherapy for non-target lesions, eg, radiotherapy, surgery, radiofrequency ablation), biologic therapy, or hormonal therapy for cancer treatment           | Should not be given whilst the patient is on IP treatment (including SoC). (Concurrent use of hormones for non-cancer-related conditions [eg, insulin for diabetes and hormone replacement therapy] is acceptable.)                                                                            |
| Immunosuppressive medications, including, but not limited to, systemic corticosteroids at doses exceeding 10 mg/day of prednisone or its equivalent, methotrexate, azathioprine, and tumor necrosis factor $\alpha$ blockers | Should not be given whilst the patient is on IP treatment (including SoC). (Use of immunosuppressive medications for the management of IP-related AEs or in patients with contrast allergies is acceptable. In addition, use of inhaled, topical, and intranasal corticosteroids is permitted. |
| Live attenuated vaccines                                                                                                                                                                                                     | Should not be given through 30 days after the last dose of IP (including SoC) during the study                                                                                                                                                                                                 |

| Rescue/supportive medication/class of drug:                                                                                                                                                                                             | Usage:                                        |
|------------------------------------------------------------------------------------------------------------------------------------------------------------------------------------------------------------------------------------------------|------------------------------------------------------|
| Concomitant medications or treatments (eg, acetaminophen or diphenhydramine) deemed necessary by the Investigator to provide adequate prophylactic or supportive care, except for those medications identified as “prohibited” as listed above | To be administered as prescribed by the Investigator |
| Best supportive care (including antibiotics, nutritional support, growth factor support, correction of metabolic disorders, optimal symptom control, and pain management [including palliative radiotherapy, etc])                             | Should be used when necessary for all patients       |
| Best supportive care (including antibiotics, nutritional support, growth factor support, correction of metabolic disorders, optimal symptom control, and pain management [including palliative radiotherapy, etc])                             | Should be used when necessary for all patients       |

## **8. STUDY PROCEDURES**

### **8.1 Schedule of study procedures**

Before study entry, throughout the study, and following study drug discontinuation, various clinical and diagnostic laboratory evaluations are outlined. The purpose of obtaining these detailed measurements is to ensure adequate safety and tolerability assessments. Clinical evaluations and laboratory studies may be repeated more frequently if clinically indicated. The Schedules of Assessments during the screening and treatment period is provided following the Protocol Synopsis

#### **8.1.1 Screening Phase**

Screening procedures will be performed up to 28 days before Day 1, unless otherwise specified. All subjects must first read, understand, and sign the IRB/REB/IEC-approved ICF before any study-specific screening procedures are performed. After signing the ICF, completing all screening procedures, and being deemed eligible for entry, subjects will be enrolled in the study. Procedures that are performed prior to the signing of the ICF and are considered standard of care may be used as screening assessments if they fall within the 28-day screening window.

The following procedures will be performed during the Screening Visit:

- Informed Consent
- Review of eligibility criteria
- Medical history and demographics
- Complete physical exam
- ECOG Performance Status
- Vitals signs, weight and height
- 12-lead ECG (in triplicate [2-5 minutes apart])
- Review of prior/concomitant medications
- Imaging by CT scan
- Tumor Biopsy with known mutational status (Kras/Nras/Braf – MSS/MSI). If initial biopsy (initial tumor or metastasis) exist with sufficient material for analysis and if patient agree to provide consent to use archived tissue, no new biopsy should be performed. If no material exist, a new biopsy should be performed.
- Clinical laboratory tests for:
  - Hematology (see Table 3)
  - Clinical chemistry (see Table 4)
  - TSH
  - Coagulation (PT, PTT, INR)
  - Creatinine Clearance
  - Serum pregnancy test (for women of childbearing potential only)
  - Hepatitis serologies
  - Urinalysis (see Table 5)

### **8.1.2 Treatment Phase**

Procedures to be conducted during the treatment phase of the study are presented in the Schedule of Assessments table 1. Screening procedures performed within J28 to J-1 of Cycle 1 Day 1.

- Complete physical exam
- ECOG Performance Status
- Weight
- Vitals signs to be performed before infusion and should also be repeated 30mn after tremelimumab and durvalumab infusion
- 12-lead ECG if clinically indicated
- Review of prior/concomitant medications
- Imaging by CT scan at Cycle 6, 12 and 18
- Clinical laboratory tests scheduled as described in the schedule of assessment:
  - Hematology (see Table 3)
  - Clinical chemistry (see Table 4)
  - TSH
  - Coagulation (PT, PTT, INR)
  - Creatinine Clearance
  - Serum pregnancy test (for women of childbearing potential only) and if clinically indicated
  - Hepatitis serologies
  - Urinalysis (see Table 5)

### **8.1.3 End of Treatment**

End of treatment is defined as the last planned dosing visit within the 24-month dosing period corresponding to Cycle 48. For subjects who discontinue durvalumab or tremelimumab prior to 12 months, end of treatment is considered the last visit where the decision is made to discontinue treatment. All required procedures may be completed within  $\pm 7$  days of the end of treatment visit. Repeat disease assessment is not required if performed within 28 days prior to the end of treatment visit.

Procedures to be conducted at the end of treatment visit are listed below:

- Complete physical exam
- ECOG Performance Status
- Vitals signs, weight
- 12-lead ECG
- Review of prior/concomitant medications
- Imaging by CT scan
- Clinical laboratory tests scheduled as described in the schedule of assessment:
  - Hematology (see Table 3)
  - Clinical chemistry (see Table 4)
  - TSH

- Coagulation (PT, PTT, INR)
- Creatinine Clearance
- Serum pregnancy test (for women of childbearing potential only) if clinically indicated
- Hepatitis serologies
- Urinalysis (see Table 5)

All subjects will be followed for survival until the end of the study regardless of further treatments, or until the sponsor ends the study.

#### **8.1.4 Explorative study**

Procedures to be conducted for the exploratory study are presented in the Schedule of Assessments on table II. Before any procedure, patients should consent to participate to the exploratory study by signing the informed consent form related to the explorative studies.

### **8.2 Description of study procedures**

#### **8.2.1 Medical history and physical examination, electrocardiogram, weight and vital signs**

Findings from medical history (obtained at screening) and physical examination shall be given a baseline grade according to the procedure for AEs. Increases in severity of pre-existing conditions during the study will be considered AEs, with resolution occurring when the grade returns to the pre-study grade or below.

Physical examinations will be performed on study days noted in the Schedule of Assessments.

#### **8.2.2 Physical examination**

Physical examinations will be performed according to the assessment schedule. Full physical examinations will include assessments of the head, eyes, ears, nose, and throat and the respiratory, cardiovascular, GI, urogenital, musculoskeletal, neurological, dermatological, hematologic/lymphatic, and endocrine systems. Height will be measured at Screening only. Targeted physical examinations are to be utilized by the Investigator on the basis of clinical observations and symptomatology. Situations in which physical examination results should be reported as AEs are described in Section 10

#### **8.2.3 Electrocardiograms**

Resting 12-lead ECGs will be recorded at screening and as clinically indicated throughout the study. ECGs should be obtained after the patient has been in a supine position for 5 minutes and recorded while the patient remains in that position.

At Screening, a single ECG will be obtained on which QTcF must be <470 ms.

In case of clinically significant ECG abnormalities, including a QTcF value >470 ms, 2 additional 12-lead ECGs should be obtained over a brief period (eg, 30 minutes) to confirm the finding.

Situations in which ECG results should be reported as AEs are described in Section 10.0.

#### **8.2.4 Vital signs**

Vital signs (blood pressure [BP], pulse, temperature, and respiration rate) will be evaluated according to the assessment schedules.

On infusion days, patients receiving durvalumab + tremelimumab treatment will be monitored during and after infusion of IP as presented in the bulleted list below.

Supine BP will be measured using a semi-automatic BP recording device with an appropriate cuff size, after the patient has rested for at least 5 minutes. BP and pulse will be collected from patients receiving durvalumab + tremelimumab treatment before, during, and after each infusion at the following times (based on a 60-minute infusion):

Prior to the beginning of the infusion (measured once from approximately 30 minutes before up to 0 minutes [ie, the beginning of the infusion]).

Approximately 30 minutes during the infusion (**halfway** through infusion).

At the end of the infusion (approximately 60 minutes  $\pm$  5 minutes).

A 1-hour observation period is required after the first infusion of durvalumab and tremelimumab.

If no clinically significant infusion reactions are observed during or after the first cycle, subsequent infusion observation periods can

be at the Investigator's discretion (suggested 30 minutes after each durvalumab and tremelimumab infusion).

If the infusion takes longer than 60 minutes, then BP and pulse measurements should follow the principles as described above or be taken more frequently if clinically indicated. The date and time of collection and measurement will be recorded on the appropriate eCRF. Additional monitoring with assessment of vital signs is at the discretion of the Investigator per standard clinical practice or as clinically indicated.

Body weight is also recorded along with vital signs.

Situations in which vital signs results should be reported as AEs are described in Section 10.3. A complete physical examination will be performed and will include an assessment of the following (as clinically indicated): general appearance, respiratory, cardiovascular, abdomen, skin, head and neck (including ears, eyes, nose and throat), lymph nodes, thyroid, musculo-skeletal (including spine and extremities), genital/rectal, and neurological systems and at screening only, height.

## 8.2.5 Clinical laboratory tests

The following clinical laboratory tests will be performed (see the Schedule of Assessments)

- Coagulation parameters: Activated partial thromboplastin time and International normalised ratio to be assessed at baseline and as clinically indicated
- Pregnancy test (female subjects of childbearing potential only)
  - Urine human chorionic gonadotropin
  - Serum beta-human chorionic gonadotropin (at screening only)
- Thyroid Stimulating Hormone
  - free T3 and free T4 only if TSH is abnormal
- Other laboratory tests
  - Hepatitis A antibody, hepatitis B surface antigen, hepatitis C antibody
  - HIV antibody

**Table 3. Hematology Laboratory Tests**

|                                           |                         |
|-------------------------------------------|-------------------------|
| Basophils                                 | Mean corpuscular volume |
| Eosinophils                               | Monocytes               |
| Hematocrit                                | Neutrophils             |
| Hemoglobin                                | Platelet count          |
| Lymphocytes                               | Red blood cell count    |
| Mean corpuscular hemoglobin               | Total white cell count  |
| Mean corpuscular hemoglobin concentration |                         |

**Table 4. Clinical chemistry (Serum or Plasma) Laboratory Tests**

|                            |                              |
|----------------------------|------------------------------|
| Albumin                    | Glucose                      |
| Alkaline phosphatase       | Lactate dehydrogenase        |
| Alanine aminotransferase   | Lipase                       |
| Amylase                    | Magnesium                    |
| Aspartate aminotransferase | Potassium                    |
| Bicarbonate                | Sodium                       |
| Calcium                    | Total bilirubin a |

**Table 4. Clinical chemistry (Serum or Plasma) Laboratory Tests**

|                                        |                                                          |
|----------------------------------------|----------------------------------------------------------|
| Albumin                                | Glucose                                                  |
| Chloride                               | Total protein                                            |
| Creatinine                             | Urea or blood urea nitrogen, depending on local practice |
| Gamma glutamyltransferase b | Uric acid                                                |

a If Total bilirubin is  $\geq 2 \times \text{ULN}$  (and no evidence of Gilbert's syndrome) then fractionate into direct and indirect bilirubin

b At baseline and as clinically indicated

**Table 5. Urinalysis Testsa**

|           |                       |
|-----------|-----------------------|
| Bilirubin | pH                    |
| Blood     | Protein               |
| Glucose   | Specific gravity      |
| Ketones   | Colour and appearance |

a Microscopy should be used as appropriate to investigate white blood cells and use the high power field for red blood cells

## 8.2.6 Patient reported outcomes (PRO) - QLQ-C30 and QLQ-CR29

The PRO questionnaires should be administered and completed at the clinic in accordance with the study plan in the schedule of events of ancillary studies. Patients must complete the QLQ-C30 and QLQ-CR29 at the same time in any order.

The instruction for completion is as follow:

- It must be completed by the patient
- It must be completed by the patient before any investigations or procedures are performed at the clinic
- Only one answer for each question
- The patients should not receive help from family, friend or clinical staff to answer the questionnaires.

## 8.3 Biological sampling procedures

### 8.3.1 Biopsy

#### 8.3.1.1 Principal study (Exome analysis and immunohistochemistry)

At screening, tissue samples from initial tumor or metastasis will be use for Exome analysis and immunohistochemistry. Archived tissue could be used if patient consent and if sufficient material for analysis is available.

- For exome analysis: 10 X 5µm thick unstained section from FFPE bloc + 1 HES blade encircling the tumor zone and estimate of the tumor cell content of the fringed area.

- For immunohistochemistry: 5 to 11 X 4µm thick unstained section from FFPE bloc

If no sufficient material is available to perform exome and immunohistochemistry, meaning a minimum of 16 to 21 unstained section in the existing block, patients will be asked to undergo a new biopsy in the context of the principal study if considered clinically appropriate by their treating physician.

⇒ **Existing archived tissue samples**

If initial biopsies samples (initial tumor or metastasis) already exist, they should be retrieving from the Bio-Bank storage location. These blocks should undergo quality review, prior to evaluation or shipment. When submitting sample for PD-L1 testing and for whole exome and RNAseq analysis, the recommendation is to ship the block for sectioning to occur at the central laboratory at Dijon. Blocks should be shipped containing enough material to be provided to allow a minimum of 11 sections of 5 micron thick for RNAseq analysis and 5-11 sections of 4µm thick each for immunohistochemistry. A total of 16-21 sections should be performed and send.

Where it is not possible or indicated to ship the block to the central laboratory in Dijon, unstained slides should be prepared from the paraffin-embedded tumor sample block (described below) prior to evaluation or shipment.

1) **10 x 5 micron (µm) thick, unstained** from initial tumor tissues or metastasis should be provided for whole exome analysis and RNAseq + **1 HES blade** encircling the tumor zone and an estimate of the tumor cell content of the fringed area. This sample will allow to:

- To determine genetically characterized for MSI status using classically determination of microsatellite instability using multiplex PCR.
- To determine NRAS, KRAS and Braf status using allelic discrimination and CIMP phenotype will be determined using bisulfitation and analysis of CpG Methylator specific marker using PCR.
- To perform identification of tumor-specific mutations, whole-exome sequencing of tumor cells and autologous healthy tissue (frozen sample) will be realized. After DNA extraction, exon capture will be performed with the use of the SureSelect Human All Exon 50-Mb kit. Enriched exome libraries will be sequenced on the local NextSeq (Illumina) platform to provide mean exome coverage of more than 100x. Only non-synonymous and indel mutations will be retained for final genomic analyses.
- We will determine candidate of neoantigens: For each case, to predict potential neoantigens from the set of non-synonymous and indel mutations. Subsequently, predictions for proteasomal processing and HLA class I binding will be performed on stretches of amino acid sequences that contained non synonymous mutations, using the NetChop Cterm3.0 and NetMHC3.2 algorithms. The number of non-synonymous mutations and candidate neoantigens will be correlated with quantitative evaluation of each immune population, response to therapy (radiological) and patients survival (DFS & OS).

- To have a more view of the local immune response RNAseq will be performed on biopsy before and after therapy and the immune contexture will be assessed in this RNA-Seq using a strategy of determination of the expression of immune metagene with normalization to normal liver tissue and a comparison of this immune contexture observer before and after therapy. Metagene analyse will involve CTL response, immune checkpoints, immune checkpoints ligand, Helper T cells response (Th1, Th2 Th9, Th17, Treg, TFH), MDSC, macrophage, dendritic cells, inflammation.

2) A minimum of **5-11 x 4 micron (µm) thick, unstained sections** should be provided and will allow to:

- study the immune cells infiltration into the tumor by immunohistochemistry staining. Immune infiltrate will be assessed by immunohistochemistry (CD3, CD8, PDL1, PD1, CTLA4, Nkp46, Foxp3, DcLamp, CD20, CD14, CD4). Such marker will inform us on the effect of the therapy on variation of T cells infiltrates, NK cells, Treg cells, Dendritic cells, MDSC). The samples will be stored at the site of patient's care and centralized at the "plateforme de Transfer en Biologie du Cancer" in the Centre Georges-François Leclerc in Dijon under the direction of [name].
- analyze PD-1 and PD-L1 (using SP263 antibody) or CTLA-4 tumor expression by IHC and PCR. The samples will be stored at the site of patient's care and centralized in the Platform of Molecular Genetics (CGFL, Dijon), under the direction of [name].
  - Quality control of samples to be used for PD-L1 testing and also for Whole exome and RNAseq analysis:
- The site pathologist prior to PD-L1 testing should assess tissue.
- Each sample should be reviewed for:
  - Adequate fixation
  - Good preservation of morphology
  - Presence of tumor tissue
  - Histopathology consistent with indication
  - Greater than 100 tumor cells are required to determine PD-L1 status – tumor cell content must be reviewed prior to testing in order for PD-L1 obtain a valid result.

➤ Sectioning instructions

Where it is not possible or indicated to ship the block to laboratory for PD-L1 testing unstained slides should be prepared from the paraffin-embedded tumor sample block as described below:

- A minimum of 5-11 x 4 micron (µm) thick, unstained sections should be provided for PD-L1 testing + a minimum of 10 x 5 micron (µm) thick, unstained should be provided for whole exome analysis and RNAseq
- A new disposable microtome blade must be used for each block to prevent contamination between Slides are stable under these conditions for 6 months.
- Patient samples
- Apply one section per slide to positively-charged Superfrost glass slides
- For PD-L1 The sections should be dried overnight between room temperature and 37°C. Do not dry sections at temperatures above 37°C.

Sections should be stored at ambient temperature and protected from light until use or shipment to testing lab by courier at ambient temperature. It is recommended that slides are cut freshly prior to PD-L1 testing and they are used within 90 days of being cut to obtain PD-L1 status

⇒ Fresh biopsy tissue samples

Fresh metastasis Biopsies (Liver metastasis will be preferable) will be performed according to the following protocol. Samples will be collected via a core needle of 18 gauge or larger or be collected as an excisional tumour biopsy sample. Where institutional practice in this setting uses a smaller gauge needle, samples should be submitted to ensure that availability of result can be achieved. Two fine needle biopsy of metastases will be performed under ultrasound scanning appliance or by their anatomical position in the tissue via a core needle of 18 gauge or larger. This type of biopsy has shown its safety in conditions similar to patients treated with antiangiogenic (Cancer 2013 Apr 1; 119 (7): 1357-1364).

The two fine needles will be stored in formalin and then Formalin fixed and paraffin embedded (FFPE) as described below:

- Fixation of biopsy samples for immune response analyze testing
  - Previously frozen tissue is not acceptable for processing to FFPE for PD-L1 testing. To fix newly acquired tissue, place immediately (within 30 min of excision) into an adequate volume of 10% v/v neutral buffered formalin (NBF). Samples should remain in fixative for 24 – 48 hours at room temperature.
  - It is vital that there is an adequate volume of fixative relevant to the tissue (at least a 10 volume excess) and that large specimens (if any) are incised prior to fixation to promote efficient tissue preservation.
- Embedding in paraffin for immune response analyze testing
  - An overnight processing schedule into paraffin is recommended
  - Below is the suggested routine overnight processing schedule:
- Storage of tumor blocks for immune response analyze testing

- FFPE blocks should be stored at ambient temperature and protected from light until shipment by courier at ambient temperature. FFPE blocks are stable under these conditions for an indefinite period. Please refer to section 8.3.1 a) for sectioning instructions

Same protocol as described above in section should be observed for sampling preparation of:

- 10 x 5 micron ( $\mu\text{m}$ ) thick, unstained for whole exome analysis and RNAseq + 1 HES blade encircling the tumor zone and an estimate of the tumor cell content of the fringed area.
- 5-11 x 4 micron ( $\mu\text{m}$ ) thick, unstained sections

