## **2.3 Exploratory objective(s)**

### **Exploratory Studies :**

- To evaluate quality of life at each cycle,
- To determine genetically characterized for MSI status,
- To determine NRAS, KRAS and Braf status,
- To study the immune cells infiltration into the tumor,
- To analyze PD-1, PD-L1, CTLA-4 expression with Ventana assay system
- To determine double labelling of Th1, Th2, Th17, Follicular helper T cells and exhausted T cells,
- To perform identification of tumor-specific mutations,
- To determine candidate of neoantigens and also prediction for proteasomal processing and HLA class I binding will be assess,
- Analyze immune response before and after treatment start,
- To assess local immune response before and after therapy,
- To study evaluation of lymphocyte reactivity to tumor antigens,
- To analyze cytokine production by T cells.

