### **8.3.1.2 Ancillary study (Immunohistochemistry)**

If patient agree to participate to the ancillary studies, a double labelling of Th1, Th2, Th17, Follicular helper T cells will be performed at 3 different time point:

- Screening
- Visit 5 (3 Months)
- Visit 12 (6 Months)

- If archival tissue samples from metastasis or initial tumor is available and sufficient to performed 6 X 4 $\mu\text{m}$  thick, unstained sections, no new biopsy is required at screening.

- If no archival tissue samples is available a new biopsy will be required at screening with the same procedure described above in the **“Fresh biopsy tissue samples” part.**

For visit 5 and 12 a new biopsy will be required in order to have enough tissue to performed a minimum of 6 X 4 $\mu\text{m}$  unstained section from FFPE block.

Double IHC procedures will be performed once validated by a pathologist. If double staining cannot be appropriately validated, single stains as those for the main study will be performed.

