### **8.3.1.3 Tissues Samples shipment**

In case of tissue limiting, we will prioritize Exome analysis and RNA-seq first, then we will address PD1, PDL1 and CD8 expression by IHC and finally we will use material to performed double staining IHC, which we estimate less important. The tumour specimen submitted to establish eligibility should be of sufficient quantity (i.e. >100 tumour cells) to allow for PD-L1 immunohistochemistry analyses.

The following fields of data should be collected from the site/institution collecting and if, indicated shipping of the samples:

- Patient identifier (ecode or unique identifier)
- Specimen identifier (written on the specimen)
- Site identifier
- Specimen collection date
- Type of specimen submitted
- Quantity of specimen
- Date of sectioning

- Archival or fresh tumor and localization (initial tumor or metastasis)
- Tumor type
- Primary tumor location
- Metastatic tumor location (if applicable)
- Fixative

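### The exploratory before/after tissue comparison has RNAseq sections allotted at screening only, and it allows an archived primary to be paired with an on-treatment metastasis

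*Protocol*

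**What the plan says.** The objective is listed among the exploratory studies (Section 2.3 and the synopsis): "To assess local immune response before and after therapy".

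**Planned comparison.** Section 8.3.1.1 says that "RNAseq will be performed on biopsy before and after therapy", "with normalization to normal liver tissue and a comparison of this immune contexture observer before and after therapy". The same section expects the immunohistochemistry markers to show the effect of therapy on immune infiltrates.

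**Tissue before therapy.** Section 8.3.1.1: "At screening, tissue samples from initial tumor or metastasis will be use for Exome analysis and immunohistochemistry". Archived blocks are accepted. Note l to the assessment schedules requires a new biopsy only when archived material is insufficient. Section 8.3.1.2 accepts archived primary or metastasis for the ancillary baseline too.

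**Tissue after therapy.** The only later biopsies are the ancillary ones at visits 5 and 12. Section 8.3.1.2 requires a new biopsy there "to have enough tissue to performed a minimum of 6 X 4 $\mu\text{m}$ unstained section from FFPE block". Inclusion criterion 12 asks ancillary participants for an accessible metastasis, and the fresh-biopsy procedure in Section 8.3.1.1 is written for metastases, preferably liver.

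**Sections.** The exome/RNAseq table in Section 8.3.1.4 has one time point, screening, with 10 x 5 µm. Visits 5 and 12 appear only in the immunohistochemistry table, with one core and 6 x 4 µm each. When tissue is short, Section 8.3.1.3 says "we will prioritize Exome analysis and RNA-seq first".

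**Survival outcome.** Section 8.3.1.1 relates mutation and neoantigen counts to "patients survival (DFS & OS").

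**The concern.** There are two separate problems, both in rules that sites and laboratories carry out and not in analysis detail.

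First, the RNAseq comparison needs tissue at two times, and the operational tables provide it at one. A site that cuts exactly what Section 8.3.1.4 lists at visits 5 and 12 produces no RNAseq sections. No later analysis can recover tissue that was not cut.

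Second, where the baseline is an archived primary and the later sample is a fresh metastasis, the within-patient change contains a primary-versus-metastasis difference. Inclusion criterion 6 admits recurrence after localized disease with or without adjuvant FOLFOX, so such a block may also predate chemotherapy that belongs to the study regimen. Normalising to normal liver does not remove this for a colorectal primary. No passage requires the same site before and after, or separates mixed pairs from matched ones.

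At stake is an exploratory result for which patients undergo two extra invasive biopsies. The 3-month primary endpoint, its decision rule and the sample size do not depend on it.

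A smaller point in the same section is that DFS is not a usable outcome here. Every patient has measurable disease (inclusion 9) that is not resectable (exclusion 34). The protocol's own endpoint is PFS (Section 9.3).

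**Working it through.** The plan gives no figure to reproduce for this comparison: no ancillary sample size, test or significance level. The check sets the tissue rules side by side, and then illustrates the possible bias.

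**1. Sections by time point (Section 8.3.1.4)**

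| Time point | Exome/RNAseq | Ancillary immunohistochemistry |
|---|---|---|
| Screening | 10 x 5 = 50 µm | 6 x 4 = 24 µm |
| Visit 5 | none listed | 6 x 4 = 24 µm |
| Visit 12 | none listed | 6 x 4 = 24 µm |

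Screening also has 5 to 11 x 4 µm for the principal study. The later allotment is 24/50 = 48% of the sequencing allotment, and all of it is for staining. Providing both would take 50 + 24 = 74 µm per visit. The 50 µm serves exome and RNAseq together, and the protocol does not split it.

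**2. Other passages that bear on this**

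- Section 8.3.1.1, fresh biopsies: lists 10 x 5 µm for exome and RNAseq, but does not assign them to visits 5 and 12.
- Section 8.3.1.2: calls 6 x 4 µm a minimum, and describes only double or single staining.
- Section 8.3.1.3: gives sequencing priority over staining when tissue is short. This does not fit an on-treatment allotment that contains no sequencing.
- Figure 2 (synopsis): the biopsy row marked at visits 5 and 12 names PCR, immunohistochemistry, exome sequencing and neoantigens. It does not name RNAseq and sets no order.

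These cannot all be followed as they stand.

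**3. Which pairs are affected**

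| Screening sample | Visit 5/12 sample | Primary-versus-metastasis mismatch |
|---|---|---|
| Archived primary | Fresh metastasis | Yes; possibly also intervening adjuvant FOLFOX |
| Archived metastasis | Fresh metastasis | No |
| Fresh metastasis | Fresh metastasis | No |

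The metastatic site of the later core comes from inclusion criterion 12 and the fresh-biopsy procedure. The visit 5 and 12 table rows name no site.

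**4. Illustration of the bias**

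All inputs are assumptions: q = share of mixed pairs; d = pure primary-versus-metastasis difference, in SDs of the paired change; n = 30 pairs; no drug effect; two-sided 5% paired t test.

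Mean change = q·d. SD = √(1 + q(1−q)d²). Noncentrality = √n · mean / SD. Critical value with 29 df = 2.045.

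| q | d | Mean | SD | Noncentrality | False-positive rate |
|---|---|---|---|---|---|
| 0 | any | 0 | 1 | 0 | 5% |
| 0.3 | 0.5 | 0.15 | 1.026 | 0.80 | 12% |
| 0.5 | 0.5 | 0.25 | 1.031 | 1.33 | 25% |
| 0.7 | 0.5 | 0.35 | 1.026 | 1.87 | 44% |
| 0.7 | 0.8 | 0.56 | 1.065 | 2.88 | 79.5%, about 80% |

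**The case against.** The best defence is that this is a drafting gap in exploratory work and that the pieces of an answer are already there. The 6 x 4 µm is a floor and not a cap, the fresh-biopsy procedure lists RNAseq sections, and Section 8.3.1.3 ranks sequencing first. A larger core could therefore yield RNA after therapy. That stands. A reader might infer from the tables that on-treatment RNAseq is impossible, but the documents support only that none is allotted at those visits and that the passages conflict.

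A reader might also infer that every before/after change is confounded by organ. The documents do not support that either: archived or fresh metastasis is accepted at screening, and those patients have no primary-versus-metastasis mismatch.

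It can further be said that Section 8.3.1.3 already records archival or fresh status and localisation, that stratifying by site could sit in an analysis plan not shown, and that nothing says mixed pairs will be pooled. The recorded field does make separation possible, and pooling is not established. What remains is that the protocol fixes the tissue sources, announces the comparison as an effect of therapy, and sets no site rule. The section allotment is a matter for the protocol in any case.

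Finally, blood immunomonitoring gives a within-patient measure free of this problem, so the trial's immunological aim does not rest on tissue alone. That is correct and limits the importance of the point.

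**Conclusion.** The point holds within limits. The protocol plans RNAseq before and after therapy, allots sections for it at screening only, and contradicts itself on sequencing at visits 5 and 12. Separately, it permits a primary-to-metastasis pairing in which the change cannot be attributed to study treatment. The affected patients are those with an archived primary at baseline; the documents do not say how many that will be.

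The false-positive rates, 5% with no mixed pairs and 12% to 80% in the settings shown, illustrate how a site difference could pass for a drug effect. They rest on assumed q, d and 30 pairs, and are not properties of any test the protocol states.

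This is worth correcting because the remedy uses material already collected. It concerns an exploratory objective only and does not touch the primary analysis. The DFS label is a separate, simple error.

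**What to change.** 1. Reconcile Sections 8.3.1.1 to 8.3.1.4 by adding the 10 x 5 µm sequencing sections to the visit 5 and visit 12 allotment, with the existing priority in Section 8.3.1.3 applied when the core is small. No new biopsy is needed. Cost: the tissue cut rises from 24 to 74 µm per visit, so small cores will leave fewer immunohistochemistry sections.
2. Make the main before/after comparison, for RNAseq and immunohistochemistry, in pairs where both samples are metastasis, identified from the localisation field in Section 8.3.1.3. Report primary-to-metastasis pairs separately. Cost: fewer pairs in the main comparison, by a number the documents do not allow one to estimate.
3. Replace DFS by PFS in Section 8.3.1.1. No cost.
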